### Allocation and blinding

After being assessed for eligibility, patients are randomly allocated to either the intervention or control group (allocation ratio 2:1). The larger sample size in the experimental group allows more variables to be tested and gives more power to detect relevant effects in the experimental intervention. Randomization is realized via an adaptive stratified sampling (i.e., minimization) through the computerized encrypted cloud-based database (electronic case report form (eCRF)), which takes into account three conditions to balance the two groups: (1) time since stroke (≥ 30 days), (2) age (≥ 20 years old), and (3) severity (≥ 2 MRC). The allocation is concealed while patients and clinicians (except those involved in the baseline assessment) are not blind to the group allocation. A sham group was excluded from the design because an earlier study has shown a superior rehabilitation effect of training with RGS over sham computer game training using the Wii gaming console [10]. Since this is a first-of-a-kind study evaluating the outcomes (see Tables 2 and 3.) of an AI platform for rehabilitation, the sample size has been determined by feasibility (3 years) and estimated by considering the monthly number of eligible inpatients and outpatients of the participating hospitals. We plan to include a total of 90 patients via the clinical partners in the consortium. Each hospital will be recruiting 30 patients, 20 in the intervention group and 10 in the control group.

**Table 2 Tab2:** Study procedure and assessment

Study procedure	Screening and baseline assessment		Control group, standard care	Intervention group, 0–3 months daily sessions of 24 min or more	Post-treatment assessment		
	Inpatients	Outpatients			3 months	6 months	12 months
Informed consent	x	x					
Medical history	Patients’ demographics MRI/CT scan when available						
Assessment: domains and scales							
Disability and impairment	Barthel Index (BI)				x	x	x
	Stroke Impact Scale (SIS)				x		x
	Fugl-Meyer Assessment of the upper limb (UE-FM)				x	x	x
	Chedoke Arm and Hand Activity Inventory (CAHAI)				x		x
	Hamilton Depression Rating Scale (HDRS)				x		x
	Visual analog score (VAS) for pain				x		x^a^
	Modified Ashworth Scale (AS) for spasticity				x^a^		x
	Fatigue Severity Scale (FSS)				x		x
	Grip force^a^				x^a^		x^a^
	Kinematics from the motion capture camera of the RGS@home system				x	x	x
	RGSwear data (paretic arm)				Continuous		
	Incidents related to use				x		x

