	Number and reason of dropouts				x		x
	Acceptability and usability Questionnaire for patients and physicians.				x	x	x
Quality of life	Stroke Specific Quality of Life scale (SSSQOL)				x		x
	Number of falls				x	x	x
	Short-Form-36 (SF-36)				x	x	x

^a^Included in the eCRF but not in the trial registry

**Table 3 Tab3:** Additional variables collected via eCRF

Assessment		3 months	6 months	12 months
Readmission	Number of outpatients that return to the hospital after discharge	x	x	x
	Reason for readmission	x	x	x
	Days of hospitalization due to readmission	x	x	x
	Costs of readmission	x	x	x
	Presence of CVA risk markers such as waist to hip ratio, smoking cessation, blood pressure, hypertension, and blood markers	x	x	x
Cost of treatment	Total cost of therapy	x		x
	Hours of therapy	x		x
	Total cost of traveling from home to hospital	x		x
	Hours of traveling from home to hospital	x		x
	Number of days of inpatient hospitalization	x		x
Quality of life	Return to work	x	x	x
	Number of formal caregiver hours per week	x	x	x
Acceptability	Number of hours of system use at home	x		x
	Number of hours technical/visits to patients’ home	x	x	x
	Number of equipment replacements	x		x
	Incidents related to use	x		x

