## Statistical method

We will perform mainly between-subject analysis by comparing the mean outcomes of the experimental group with the mean outcomes of the control group. To analyze the clinical outcomes related to disability and impairment, we will calculate the normalized improvement, which shows improvement or decline in proportion to the maximum score possible in the respective scale, therefore avoiding ceiling effects. Depending on whether the data is following a normal distribution, we will use parametric or non-parametric statistics. In the case of non-normal data, medians will be reported. We will perform an intention-to-treat analysis. The last observation carried forward analysis will be performed alongside a complete-case analysis to account for missing data.

To address the *primary outcome on disability and impairment*, a between-subject analysis will be used to compare the change in disability (Barthel Index (BI)) between the experimental and control groups at baselines 3, 6, and 12 months.

For the *secondary outcomes* on usability and impairment and other planned comparisons, we will perform the following analysis (for abbreviations, see Table 2):

Changes in independence (CAHAI), participation (SIS), depression (HDRS) fatigue (FSS), pain (VAS), spasticity (mAS), and impairment (BI and FM-UE) are analyzed from baseline to months 3 and 12.

We will also look at the change in grip force and correlate it with FM-UE, CAHAI, and BI from baseline to 3 months and 12 months. The outcomes of this measure are important to evaluate the clinical effectiveness of the RGS intervention to reduce disability and impairment. To measure quality of life, we compare the group changes in the quality of life (SSQOL) and well-being (SF-36) from baseline to 3 months and 12 months. We will also compare well-being (SF-36) at 6 months.

For the additional variables shown in Table 3, we will proceed as follows:

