*Readmission*: We compare between the groups the number of outpatients that return to the hospital after discharge to at-home status, including readmission due to complications unrelated to stroke, from baseline to 3, 6, and 12 months. We also compare the days of hospitalization and their associated costs. Here, we will take into account the presence of CVA risk markers as covarying variables. The readmission outcome is used to evaluate the effectiveness of the RGS intervention in reducing, or at least not increasing, a hospital’s readmission after discharge compared to standard care.

*Cost of treatment*: We compare the total cost of rehabilitation therapy/hour provided at the hospital or in the community and transportation costs/hour between the hospital and home at 3 months and after 12 months. We also compare days/hours of hospitalization and whether additional therapy, not replacing the RGS-based training (e.g., magnetotherapy, electrotherapy, thermotherapy), was provided. These outcomes allow us to evaluate the RGS’s effectiveness to reduce the cost of treatment.

*Quality of life*: We will compare between the groups the number of falls reported at 3 months and 12 months. In addition, we will compare how many patients were able to return to work and how many hours professional care was provided at 3 and 12 months. These outcomes facilitate the evaluation of the impact of the RGS ecosystem on quality of life and evaluate any risks arising from using the RGS system at home.

*Acceptance*: We will assess the RGS@home use (hours) after 3 months, 6 months, and 12 months. In both groups, we will keep track of the dropouts of the study. Specifically, in the intervention group, we will analyze the use of RGS at the hospital and home and the use of RGSwear. Concerning RGS@home, we will analyze the support needed (hours and visits to the patient’s home, replacement of materials, instructions, troubleshooting, etc.) and any incidents reported by the users. Also, we will analyze the patient’s evaluation of the System Usability Scale. The outcomes of this domain are important to evaluate the acceptance of the RGS ecosystem within the experimental group and the feasibility of the system for future use.

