### Harms

The RGS system has obtained approval as a medical device that can be safely used in humans (approval obtained by *Agencia Española de Medicamentos y Productos Sanitarios, record number 792/20/E.C., and registered in EUDAMED, CIV-21-03-035989*). The approval process required an in-depth risk-benefit analysis, which classified the RGS system as a low-risk device. Nevertheless, we will collect and analyze all incidents, falls, reasons for readmissions, and reasons for dropout during the study, whether related or unrelated to the use of the devices. We do not foresee any reason to stop the trial. However, if any major incidents occur that pose a risk to the participating patients, the project leader can stop the trial.

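### Falls are recorded at 3, 6 and 12 months, but the only group comparison described uses the 3- and 12-month reports, and the counting period is not stated

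*Protocol article*

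**What the plan says.** Table 2 (under Allocation and blinding) has a row "Number of falls" marked at 3, 6 and 12 months. The quality-of-life paragraph of Statistical method then fixes the between-group comparison as one of "the number of falls reported at 3 months and 12 months". That paragraph gives two purposes for its comparisons, namely the effect on quality of life and the risks of home use. The Harms section says "we will collect and analyze all incidents, falls, reasons for readmissions, and reasons for dropout during the study", whether or not the event is related to the devices.

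Three other variables show the same pattern:

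- "Return to work" and "Number of formal caregiver hours per week" are marked at 3, 6 and 12 months in Table 3, and the quality-of-life paragraph compares them at 3 and 12 months.
- UE-FM, a named secondary outcome, is marked at all three visits in Table 2, while Statistical method states that "impairment (BI and FM-UE) are analyzed from baseline to months 3 and 12".

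The article nowhere defines the period that a falls report covers.

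**The concern.** Statistical method names 6 months where it wants that visit: for the primary Barthel Index comparison, SF-36, readmission and RGS use. A reader will therefore take 3 and 12 months as the planned set for falls, and no reason is given for leaving out the middle report. Falls are an event count and not a status at a visit, so whether omitting a report loses information depends on what each report counts. What is at stake is one of the few stated safety comparisons of a device used at home. It might not cover the whole follow-up, although the data for all of it are scheduled and the Harms section undertakes to analyse all falls.

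**Working it through.** **Inputs from the article**

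- Falls reports: 3, 6 and 12 months (Table 2).
- Reports used in the group comparison: 3 and 12 months (Statistical method, quality-of-life paragraph).
- Follow-up: 12 months from baseline.
- Counting period of a report: not given, so both natural readings are worked through.

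The article gives no figure of its own on this point to reproduce.

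**Step 1: schedule against analysis.** Falls, return to work, caregiver hours and UE-FM are all collected at 6 months (4 of 4). None has a 6-month comparison named (0 of 4).

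**Step 2: follow-up covered by the falls comparison.**

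- *Reading A, falls since the previous visit.* The 3-month report covers months 0 to 3, the 6-month report months 3 to 6, and the 12-month report months 6 to 12. The 3- and 12-month reports together cover 3 + 6 = 9 months. Left out: 12 − 9 = 3 months, and 3/12 = 25%.
- *Reading B, falls since baseline.* The 12-month report covers months 0 to 12. Left out: 0 months, 0%.

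**Step 3: effect on precision.** Assume a constant fall rate λ, Poisson counts, n patients in an arm, and T months observed per patient. The expected count is nλT, and the standard error of the estimated rate is √(λ/(nT)). Taking the 3- and 12-month reports together:

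- Reading A: SE(9 months)/SE(12 months) = √(12/9) = 1.155, about 15% larger.
- Reading B: √(12/12) = 1.00, no change.

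The same ratio applies to the log rate ratio between arms, because T changes equally in both. If falls cluster within patients, the between-patient part of the variance does not shrink with T and the inflation is smaller. About 15% is therefore the upper end for the pooled reports under a constant rate.

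**Step 4: the two sections side by side.** Harms undertakes to collect and analyse every fall. Statistical method describes a comparison at two of three reports. Harms does not say that its analysis is a comparison between groups, nor that it is done at each visit. Both statements can be true, but the reader cannot tell whether any group comparison includes the falls of months 3 to 6.

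**The case against.** The strongest reply is that no fall goes unanalysed. The Harms commitment covers all of them, and a descriptive harms summary can stand beside a two-visit comparison. This stands. A reader might infer that the two sections contradict each other, or that the plan discards safety data. The text supports neither: the first because the commitments are compatible, the second because under cumulative counting nothing is missing. What the reply leaves open is the between-group question, which is how the quality-of-life paragraph proposes to judge risk.

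It can also be said that collecting a variable at a visit does not oblige anyone to test it there, and that comparing at the end of the 3-month intervention and at the last visit is a defensible choice. For UE-FM, return to work and caregiver hours this stands. Caregiver hours are recorded per week, and return to work can be read as a status at the visit, so no loss is shown for either. Adding 6-month tests would lengthen an already long list in a trial of 90 patients.

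For UE-FM a reader might go further and claim that efficacy data are lost. Three things weigh against that:

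- The sentence that lists UE-FM at months 3 and 12 also lists the Barthel Index, which the paragraph before it compares at 6 months as well. The list is therefore not clearly exclusive.
- The planned last-observation-carried-forward analysis would bring in a 6-month value when the 12-month value is missing (not so in the complete-case analysis).
- A precision gain cannot be claimed. With an assumed within-patient correlation of 0.7, the variance factor (1 + (k − 1) × 0.7)/k is 0.85 for k = 2 visits and 0.80 for k = 3, a ratio of 0.94. That describes an average over visits. The plan compares change to month 3 and change to month 12, and a further visit leaves the precision of each unchanged.

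Finally, the choice of count model is something an article may leave to the full protocol or analysis plan. That is fair. The point here is the choice of reports, which the article does fix.

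**Conclusion.** The point holds for falls, as a matter of consistency with a modest consequence. The described group comparison uses two of three scheduled reports and may leave out between 0 and 25% of the follow-up, depending on a counting period that the article does not give. The matching increase in the standard error of the fall rate runs from none to about 15%, assuming a constant rate and taking the two reports together. Statistical method and Harms should be brought into agreement. For UE-FM, return to work and caregiver hours, the role of the 6-month data is unstated, but no loss is demonstrated. Nothing here affects the primary analysis, the sample size or the error rate.

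**What to change.** 1. State what a falls report counts, since the previous visit or since baseline, and confirm that the three hospitals record it in the same way.
2. Replace the 3- and 12-month falls comparison with one between-group comparison of the fall rate over the full follow-up. Use the 3-, 6- and 12-month reports in a Poisson or negative binomial model with log time at risk as the offset. If reports are cumulative, take the last available count or difference successive counts; do not add them up. The offset also deals with patients who leave early.
3. Refer to this analysis in Harms, so that both sections describe the same treatment of falls.
4. Say that the 6-month UE-FM, return-to-work and caregiver-hours data are descriptive.

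The cost is wording only. The data are already scheduled, and one rate comparison replaces two visit-specific ones, so no test is added.

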### Harms

The RGS system has obtained approval as a medical device that can be safely used in humans (approval obtained by *Agencia Española de Medicamentos y Productos Sanitarios, record number 792/20/E.C., and registered in EUDAMED, CIV-21-03-035989*). The approval process required an in-depth risk-benefit analysis, which classified the RGS system as a low-risk device. Nevertheless, we will collect and analyze all incidents, falls, reasons for readmissions, and reasons for dropout during the study, whether related or unrelated to the use of the devices. We do not foresee any reason to stop the trial. However, if any major incidents occur that pose a risk to the participating patients, the project leader can stop the trial.

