**Methods:**

The RGS@home study is a randomized longitudinal clinical trial designed to assess whether the combination of the RGS intervention with standard care is superior to standard care alone for the functional recovery of stroke patients at the hospital and at home. The study is conducted in collaboration with hospitals in Spain, Sweden, and France and includes inpatients and outpatients at subacute and chronic stages post-stroke. The intervention duration is 3 months with assessment at baseline and after 3, 6, and 12 months. The impact of RGS is evaluated in terms of quality of life measurements, usability, and acceptance using standardized clinical scales, together with health economic analysis. So far, one-third of the patients expected to participate in the study have been recruited (*N* = 90, mean age 60, days after stroke ≥ 30 days). The trial will end in July 2023.

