### Intervention and control groups

As explained in the “Allocation and blinding” section, patients are allocated in a randomized fashion either to the intervention group (RGS treatment plus rehabilitation as usual) or to the control group (standard care) (see Fig. 3 and Tables 2 and 3).

The *intervention group* follows a rehabilitation program for motor training using the RGS system at the clinic and home in addition to standard care. The training consists of various RGS-based exercises involving reaching, grasping, and placing virtual objects in a virtual environment. The training period and the number of training sessions are variable. They are set by the treating clinicians based on the patients’ needs and on dosage guidelines agreed by the three clinical partners in the trial (see the “Treatment dosage” section). Patients recruited at the subacute phase (inpatients) will receive the rehabilitation treatment via RGS at the hospital, from recruitment until discharge. In addition, the patients in the intervention group are prescribed occupational or physical therapy following the local clinical practice of the rehabilitation unit from admission to discharge. Patients recruited after discharge (outpatients) will train with RGS at their homes daily for 3 months, including weekends. All the patients in the intervention group (inpatient and outpatient) receive the RGSwear at recruitment for up to 1 year post-recruitment.

The *control group* receives standard care provided to patients after clinical discharge, which varies according to the patients’ condition and the different standards of care practiced in each EU country [18]. Also, at discharge, patients are provided advice for continuing voluntary rehabilitation in their homes. Given the huge regional variability, a detailed description of standard care is not reported in this study. In the footnote, we have provided the links to the National Health guidelines for Spain^1^, France^2^, and Sweden^3^.

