## Data collection and management

The clinical outcome measurements and the patients’ data are collected by each participating hospital by blinded clinicians and logged in the eCRF. Data obtained through the interaction with the RGS ecosystem is automatically logged in the MIMS. The data in the eCRF is securely stored and anonymized (patients are assigned an ID), and monitoring is organized by each clinical partner independently, adhering to local standards and procedures. To ensure all data is logged correctly and no duplicates exist, the RGS@home eCRF process automatically checks to ensure that the logged scores of the clinical scales and tests are valid. Two workshops have been organized with the study coordinators to understand how the assessments are performed and the data collected.

The data obtained from the interaction with the RGS ecosystem (kinematic data, prescriptions, protocol events, and use) is automatically stored in the MIMS, a secured cloud-based database that the participating hospitals can access via a web browser with a username and password. Within the MIMS, and separately from the eCRF, the participating hospitals can create profiles (anonymized) for each patient, determine and manage the prescriptions of exercises, and track the patient’s progress through dashboards, graphics, and analytic reports. The sponsor can remotely access the password-protected data in the MIMS to analyze the interaction with the RGS system.

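### Incidents and dropout reasons are scheduled at 3 and 12 months only, skipping the existing 6-month visit, although the Harms section promises to collect all of them throughout the study

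*Protocol article*

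**What the plan says.** The abstract sets the calendar: "The intervention duration is 3 months with assessment at baseline and after 3, 6, and 12 months". Within it, the row "Incidents related to use" appears in Table 2 and again in Table 3 (variables collected through the eCRF, under Acceptability). Both times it is marked at 3 and 12 months. The Table 2 row "Number and reason of dropouts" is marked at the same two points. By contrast, "Number of falls" in Table 2 and "Reason for readmission" in Table 3 are marked at 3, 6 and 12 months.

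The Harms section is wider than the tables. It undertakes to collect and analyse every incident, fall, cause of readmission and cause of dropout over the course of the study, whether or not a device is implicated. The one stopping provision stands in the same section: "if any major incidents occur that pose a risk to the participating patients, the project leader can stop the trial".

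Device contact does not end at month 3. Under Intervention and control groups, all intervention patients "receive the RGSwear at recruitment for up to 1 year post-recruitment". The Acceptance paragraph of the Statistical method section assesses hours of RGS@home use at 3, 6 and 12 months. Under Data collection and management, "monitoring is organized by each clinical partner independently, adhering to local standards and procedures". Data monitoring allows the sponsor to extract eCRF data four times a year, for preliminary analyses and reporting.

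**The concern.** The tables and the Harms section do not describe the same data collection. The Harms section implies complete capture over 12 months, regardless of relatedness. The tables give two time points, and the incident row is restricted to those connected with use. That restriction also leaves unclear what would be recorded for a control patient, who has no RGS to use.

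The harms data are what is at stake. If sites follow the tables literally, an incident soon after the 3-month visit is next asked about at month 12, and its record depends on what the patient remembers. Some patients may enter with moderate to severe non-fluent aphasia (Table 1), which makes recall at a distance less dependable. Dropout reasons matter here as well, because a device problem is one possible reason for leaving. Undercounting after month 3 would make the system look safer at home than it is, in a trial that counts the risks of home use among its questions.

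**Working it through.** No sample size, power or event rate enters this point, and the article states no interval to reproduce. The check sets the scheduled points side by side and subtracts consecutive ones.

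| Item | Where | Scheduled at (months) | Longest gap |
|---|---|---|---|
| Incidents | Tables 2 and 3 | 3, 12 | 12 - 3 = 9 |
| Dropouts and reasons | Table 2 | 3, 12 | 12 - 3 = 9 |
| Falls | Table 2 | 3, 6, 12 | 12 - 6 = 6 |
| Readmission reasons | Table 3 | 3, 6, 12 | 12 - 6 = 6 |

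1. *First interval.* From baseline to the first point is 3 - 0 = 3 months for all four items, which equals the stated length of the intervention.
2. *Second interval.* For incidents and dropout reasons it runs from month 3 to month 12. That is 9 of 12 months, or 75% of follow-up, and all of the time after the 3-month intervention.
3. *Exposure in that interval.* The wearable stays for up to 12 months, so up to 12 - 3 = 9 months of wearable exposure fall inside the gap. RGS@home hours are also to be assessed at 6 and 12 months.
4. *Effect of using the 6-month visit.* The longest scheduled gap would fall from 9 to 6 months, the same as for falls and readmission reasons. Entry when the site learns of an event would make the visit question a backstop.
5. *Scope.* The Harms section covers events related and unrelated to the devices. The table row covers only those related to use. The two differ in content as well as timing.
6. *Link to the stopping provision.* It refers to major incidents. Dropout reasons do not trigger it, and it is not tied to any visit or extract. The 9-month figure therefore describes the data schedule. It is not a delay in the provision.

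**The case against.** A reader might infer that an event can go unrecorded for up to 9 months and that the stopping provision therefore cannot act in time. The article does not support this. The tables list assessment points and do not forbid reporting between them. The Harms section commits to collection during the whole study, and the Acceptance paragraph speaks of incidents reported by users and of tracking dropouts in both groups, with no time point attached. The project leader's power to stop waits for neither a visit nor an extract. How an urgent incident reaches the project leader is reporting procedure, which a condensed article commonly leaves to the full protocol. That protocol exists, since the article offers it on request, but it is not shown. Its silence here is no finding. Counts of patients enrolled during a supposed delay, or chances that one hospital would notice a device problem, would rest on the same unsupported premise.

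Other safeguards exist. Falls and readmission reasons, two ways in which a serious event could surface, are collected at 6 months. The Adherence to treatment section describes continuous monitoring and clinician contact when adherence is low, and the sponsor can see usage data in the MIMS. The dropout cell at month 12 may also be a tally of those who left since month 3, with no patient asked to recall anything.

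All of this stands against the stronger reading. It does not remove the mismatch. Usage monitoring applies to the intervention arm and is not adverse-event reporting. The blank 6-month cells remain in a stated schedule, beside rows that use the same visit, and the article does not say whether incidents and dropouts are logged as they occur.

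**Conclusion.** The point holds as a fault in the stated schedule and a mismatch with the Harms section. Incidents and dropout reasons have a longest scheduled gap of 9 months, 3 months more than falls and readmission reasons, and they skip a visit that already takes place.

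The consequence is conditional. If capture happens only at the scheduled points, incidents after month 3 depend on long recall and may be undercounted. The article gives no figure from which to estimate by how much. If sites log events as they learn of them, the loss is small and the tables merely fail to say so. In neither case does the article show that events go unrecorded or that the stopping provision fails, and the stopping criterion itself is not judged here. The change is worth making because it improves harms ascertainment at almost no cost.

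**What to change.** Change Tables 2 and 3 so that incidents, related or unrelated to the devices, and dropouts with their reasons are entered in the eCRF when the site learns of them. They should also be asked about at 3, 6 and 12 months in both arms. Reword the row labels and the Harms section so that scope and timing agree. Add to the existing quarterly extract one tabulation, pooled over the three hospitals, of incidents, falls, readmissions and dropouts.

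The 6-month visit, the eCRF and the extract are already in place, so the cost is an edit to the eCRF schedule and slightly more data entry at the sites. The stopping provision is left as it is.
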